**Figure 2. F2:**
[figure not shown]
Study flow diagram. CRCEI: Community Resilience and Collective Efficacy Intervention; HT: Health Topic Comparison.

#### Site Eligibility Criteria, Selection Process, and Study Setting

This study includes 8 neighborhood sites in the greater Pittsburgh, Pennsylvania, region. Four neighborhoods were initially chosen as intervention sites based on having high levels of gun and community violence incidents and desiring or engaged in efforts to increase community safety and identified as priority neighborhoods by the Allegheny County Department of Human Services, Office of Behavioral Health, interested community partners, and the project Steering Committee. The Steering Committee guides and informs the project and includes community partners, resident facilitators, interdisciplinary and countywide partners, and research team members.

To identify 4 comparison sites, the team used a process we refer to as, “participatory propensity score matching.” Building on the work of the abovementioned stakeholder groups, the research team constructed a list of 29 additional neighborhoods that were similarly high in violence. Steering Committee members then rated the identified neighborhoods in terms of appropriateness and need, recommending the removal of 5 neighborhoods that were least comparable. The research team then calculated propensity scores for the remaining 24 neighborhoods.

Wilkinsburg	4	11,212	75.40	44.15	9.15	4.10	24.15	20.53	12.48
Comparison neighborhoods									
California Kirkbride, Manchester (city)	1	2864	75.40	29.10	4.20	4.90	12.30	15.80	10.90
East Hills (city)	1	2777	86.50	45.30	6.10	9.50	17.80	27.10	19.40
Turtle Creek	1	5161	40.00	38.80	9.60	4.40	23.30	22.40	17.30
Duquesne	3	5534	65.10	44.23	11.80	4.43	11.47	31.07	21.73

Within each neighborhood, a different organization works with the research team on the project. In the intervention neighborhoods, community partners whose mission, goals, and programs align with the project are engaged through a formal agreement and scope of work and receive funds to pay for identified staff to work with the research team on the project. In the comparison sites, a community organization is identified that can host and inform the health sessions and is given a stipend to assist with covering the time and effort for hosting the sessions at their facility. Community partners in the intervention neighborhoods include community development organizations, grassroots organizations working to promote safety and provide support for victims of violence and their families, or other neighborhood-based organizations working to improve community outcomes. In addition, 3 residents are hired as community facilitators in the intervention neighborhoods based on their engagement with youth and/or adult residents and in local safety and community organizing and improvement efforts. Community organizations hosting health sessions in the comparison communities include faith-based organizations, community centers, neighborhood associations, and libraries. Asset maps are created for each intervention and comparison neighborhood with the goal of identifying community champions and relevant resources to support the project. The research team relies on partnerships with key constituents in each of these sites (including site coordinators, facilitators, partners, and community members) to facilitate recruitment and retention as described below.

### Outcome Measures

#### Primary Outcome Measure

Table 2 contains a description of the primary and secondary outcome measures (Table 2). The primary outcome is self-reported collective efficacy at the individual participant level across 3 points in time (ie, T1, T2, and T3). *Collective efficacy* is measured with the 10-item Collective Efficacy Scale, which has been previously validated and widely used, including among low-income, African American, and youth samples [28,34,35]. The measure includes a 5-item “social cohesion and trust” subscale and a 5-item “informal social control” subscale. Each item is assigned values based on a 5-point Likert-style scale, and final scores are calculated by averaging responses across items (range 1‐5).

**Table 2. T2:** Primary and secondary outcome measures.

Outcomes	Measures description	Time frame
Primary outcome		
Neighborhood collective efficacy (28, 34, 35)	Informal social control: How likely is it that your neighbors can be counted on to “do something” if.... Children were skipping school and hanging out on a street corner, Children were spray-painting graffiti on a local building. Children were showing disrespect to an adult, A fight broke out in front of their house, and someone was being beaten or threatened; The fire station closest to your house was going to be closed down by the city because of budget cuts, Youth are vandalizing or stealing a car in the neighborhood, and Someone is vandalizing your neighbor’s property. Five-point Likert scale from very likely to very unlikely. Social cohesion: Please indicate how strongly you agree or disagree with the following statements: People around here are willing to help their neighbors, This is a close-knit neighborhood, People in this neighborhood can be trusted, People in this neighborhood generally don’t get along with each other, and People in this neighborhood do not share the same values.” Five-point Likert scale from Strongly Agree to Strongly Disagree	Community survey T1 and T3; and participant survey T1, T2, and T3
Secondary outcomes		
Willingness to intervene (36)	How likely would you intervene in or “do something” about the following potential problems in your neighborhood? (Same items and Likert Scale as the Informal Social Control scale)	Participant survey T1, T2, and T3
Social connections (neighborhood integration) (10)	How many adults (age 18 and over) in your neighborhood… Do you know by sight? Do you know by name? Do you talk to on a regular basis? How many young people (less than age 18) in your neighborhood…Do you know by sight? Do you know by name? Do you talk to on a regular basis? Ordinal range (None (0), A few (1-5), Some (6-10), A lot (over 10))	Community survey T1 and T3; and participant survey T1, T2, and T3
Community norms, values, and attitudes about intervening (10)	How strongly do you agree or disagree with the following statements about your neighborhood? It is appropriate to question strangers in your neighborhood, It is appropriate to intervene in suspicious behaviors in your neighborhood, It’s OK to say something if someone is behaving inappropriately in your neighborhood, Good neighbors mind their own business, When neighbors intervene, neighborhoods are safer, I can identify behaviors that most of my neighbors would disapprove of, People in my neighborhood would support someone if they intervened in inappropriate behavior in the neighborhood, Personally assisting people in trouble is very important to me, The police play an important role in preventing crime in this neighborhood, It is the job of the police, not residents, to deal with inappropriate neighborhood behavior. Five-point Likert scale from strongly agree to strongly disagree.	Community survey T1 and T3; and participant survey T1, T2, and T3
Exposure to violence (37)	Composite measure comprised of Exposure to Violence and Witness to Violence to measure number of individual-level events of violence exposure. Response: Yes or No Exposure to violence: The next section asks about your personal experiences with violence in your neighborhood. Have you…been chased when you thought that you could really get hurt? been hit, slapped, punched, or beaten up? This does not include fooling around? been attacked with a weapon, like a knife or a bat? This does not include getting shot or shot at? been shot? This does not include being shot with any type of toy gun (ex. BB gun, paint gun, airsoft gun, pellet gun, etc.), been shot at, but not wounded? had someone threaten to seriously hurt you, other than what you have already shared? This includes being threatened with a weapon? seen a dead body? been told that someone you knew had been shot, but not killed? been told that someone you knew had been killed? Witness to violence: The next section asks whether you have seen someone else hurt by violence in your neighborhood. Have you… seen someone else get chased when you thought they could really get hurt? seen someone else get hit, slapped, punched or beaten up? This does not include when they were playing or fooling around, seen someone else get attacked with a weapon, like a knife or a bat? This does not include getting shot or shot at, seen someone else get shot? This does not include being shot with any type of toy gun (ex. BB gun, paint gun, airsoft gun, pellet gun, etc.), seen someone else get shot at, but not actually wounded? seen someone else get killed as a result of violence, like being shot, stabbed, or beaten to death? seen a gun in your neighborhood? heard gun shots in your neighborhood?	Community survey T1 and T3; and participant survey T1, T2, and T3
Neighborhood collective efficacy (26)	At the neighborhood level, we measure collective efficacy, using the same measure of collective efficacy described above. It is aggregated to a mean value based on responses among all participants within a given neighborhood on the community survey.	Community survey T1 and T3
Violent crime data	Pittsburgh Bureau of Police open data portal; Pennsylvania Uniform Crime Reporting (UCR) system and Allegheny County sources, including police blotter data and the county’s integrated data warehouse.	Community survey T1 and T3

#### Secondary Outcome Measures

The evaluation has 2 groups of secondary outcomes, those at the participant level and those at the neighborhood level. Intermediary, individual-level beliefs and behaviors related to collective efficacy are measured, including participants’ willingness to intervene, social connections, and prointervening norms and values. *Willingness to intervene* is a modified version of the Collective Efficacy social control subscale, with questions focusing on whether the participant is likely to intervene in social problems (ie, in lieu of whether they perceive their neighbors as being willing to intervene) [36]. *Social connections* are measured via 3 questions asking how many neighbors (youth and adults) that participants know by sight, name, and talking to on a regular basis (range 0 to >10). *Community norms, values and attitudes about intervening* is a scale asking participants the degree to which they agree with 10 statements related to norms and values pertaining to intervening in social problems [10]. *Exposure to violence* [37] is measured using 17 items with binary yes or no response options, including 9 items capturing *direct exposure* to violence and 8 items capturing *indirect exposure* to violence (ie, witnessing violence). This exposure to violence measure has been previously validated [37]. Exposure to violence values are calculated by the proportion of respondents endorsing each item (ie, responding “yes”). These data are collected from residents in the intervention and comparison neighborhoods via the community survey and at 2 time points, baseline and follow-up.

At the neighborhood level, we measure *collective efficacy* using the same measure of collective efficacy described earlier [26], which is aggregated to a mean value based on responses among all participants within a given neighborhood on the community survey. Prior research uses self-reported survey measures to measure collective efficacy at the individual and neighborhood levels. We measured collective efficacy at the individual level by surveying participants in the intervention and comparison sessions. We also measured collective efficacy at the neighborhood level through our community survey, and similar to Sampson et al, the responses are aggregated to the neighborhood level.

Finally, violent crime data for City of Pittsburgh neighborhoods are obtained from the Pittsburgh Bureau of Police open data portal, while data for municipalities outside the city (eg, Wilkinsburg, Duquesne, Turtle Creek, and Braddock) are drawn from the Pennsylvania Uniform Crime Reporting system and Allegheny County sources, including police blotter data and the county’s integrated data warehouse.

### Sample Size and Power

For the primary outcome in aim 1, individual-level neighborhood collective efficacy, the necessary sample size was calculated based on traditional methods that assume a fixed number of clusters. Using a 2-sided alpha of .05 and small-sample cluster-robust adjustments with 6 degrees of freedom, the study achieves 80% power to detect meaningful effects at the individual level. Specifically, the trial can detect a standardized mean difference of about 0.66 when the intraclass correlation coefficient (ICC) is 0.05. Under more conservative assumptions, the detectable effect size is approximately 0.83 when the ICC is 0.10 and 1.10 when the ICC is 0.20. These values highlight that the study is positioned to identify moderate to large individual-level intervention effects. By quantifying these detectable ranges, the trial not only clarifies its current analytic capacity but also establishes concrete guidance for future community trials, where additional neighborhoods or larger enrollments could be used to target smaller effects of substantive interest.

For aim 2, which evaluates neighborhood-level outcomes such as collective efficacy and community violence, the unit of comparison is the neighborhood. The study includes 8 neighborhoods: 4 assigned to the intervention and 4 to the comparison. With 8 clusters, the design is best suited to identifying larger neighborhood-level effects, which ensures that any observed changes will be both meaningful at the community scale and informative for the field. Using a 2-sided alpha of .05 and small-sample cluster-robust adjustments with 6 degrees of freedom, the minimum detectable effect size was estimated. Without adjustment for baseline, the detectable standardized effect is approximately 1.8. As aim 2 analyses will adjust for baseline neighborhood measures, precision improves as the correlation between baseline and follow-up increases. For plausible baseline–follow-up correlations, the detectable effect sizes range from approximately 1.9 when the correlation is 0.60, to 1.7 when the correlation is 0.70, to 1.4 when the correlation is 0.80, and to 1.2 when the correlation is 0.85. Reporting these estimates provides a transparent picture of what can be inferred from this trial and creates clear parameters for planning future evaluations, where additional neighborhoods would allow the detection of smaller, yet still important, community-level changes.

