In summary, this study protocol outlines the initial quasi-experimental evaluation of an ongoing federally funded collective efficacy intervention. Findings may provide urgently needed information about the effectiveness of a strengths-based program that focuses on resiliency building and collective efficacy for communities impacted by violence that is an alternative to deficit-based, punitive, and carceral approaches. The intervention and its results will also inform community interventions and policies that promote safe, supported, and connected communities and build their capacity for sustainable community change. Lessons learned with this evaluation also guide the implementation of an ongoing cluster-randomized controlled trial of the novel CRCEI in 12 additional communities in the Pittsburgh region.

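### The aim 2 detectable effect without baseline adjustment should be about 2.3 to 2.4, not 1.8; power at 1.8 is about 57%

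*Protocol article*

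**What the plan says.** The aim 2 paragraph of Sample Size and Power in the protocol article fixes the design: "the unit of comparison is the neighborhood", and "The study includes 8 neighborhoods: 4 assigned to the intervention and 4 to the comparison". The test is two-sided at .05, with "small-sample cluster-robust adjustments with 6 degrees of freedom, the minimum detectable effect size was estimated".

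The results follow. First the unadjusted one: "Without adjustment for baseline, the detectable standardized effect is approximately 1.8". The text then says that, because the aim 2 analyses adjust for baseline, "precision improves as the correlation between baseline and follow-up increases", and that "the detectable effect sizes range from approximately 1.9 when the correlation is 0.60", falling to 1.7 at 0.70, 1.4 at 0.80 and 1.2 at 0.85.

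The power target appears only in the preceding aim 1 paragraph, where "the study achieves 80% power to detect meaningful effects at the individual level". The aim 2 paragraph does not repeat it.

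**The concern.** The conflict can be seen without calculation. With the degrees of freedom held at 6, adjusting for a baseline that correlates 0.60 with follow-up removes residual variance and must lower the detectable effect. The paragraph has it rising from 1.8 to 1.9, so at least one of the two figures is wrong.

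The authors present these numbers as an account of what the trial can show and as planning parameters for later evaluations. If 1.8 is the wrong one, a team that plans an unadjusted comparison of 4 versus 4 communities from it would fall well short of its intended power. The text would also make baseline adjustment, which is the planned primary analysis for aim 2, look useless or harmful at a correlation of 0.60.

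**Working it through.** **Inputs, from Sample Size and Power**
- 4 intervention and 4 comparison neighborhoods, with the neighborhood as the unit
- two-sided alpha .05, 6 degrees of freedom
- power 80% (stated for aim 1, assumed for aim 2 and tested below)
- effect in units of the between-neighborhood standard deviation (assumed; the adjusted figures fit this scale)

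**Step 1. Unadjusted detectable effect.** The standard error of the difference, in SD units, is √(1/4 + 1/4) = 0.7071. The critical value t(.975, 6) is 2.447.
- t plus z: (2.447 + 0.842) × 0.7071 = 2.325
- t plus t: (2.447 + 0.906) × 0.7071 = 2.371
- exact noncentral t at 80% power: 2.381

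None of these is near 1.8.

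**Step 2. Reproduce the adjusted figures.** Multiply the unadjusted value by √(1 − r²).

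| r | √(1 − r²) | From 2.325 | Stated | From 1.8 |
|---|---|---|---|---|
| 0.60 | 0.800 | 1.86 | 1.9 | 1.44 |
| 0.70 | 0.714 | 1.66 | 1.7 | 1.29 |
| 0.80 | 0.600 | 1.40 | 1.4 | 1.08 |
| 0.85 | 0.527 | 1.22 | 1.2 | 0.95 |

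The base of 2.325 reproduces all four stated figures to rounding, which also supports the 80% target. A base of 1.8 reproduces none.

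**Step 3. Work backward.** Dividing each stated adjusted figure by √(1 − r²), and allowing ±0.05 for rounding, gives these ranges for the unadjusted value:
- r = 0.60: 2.31 to 2.44
- r = 0.70: 2.31 to 2.45
- r = 0.80: 2.25 to 2.42
- r = 0.85: 2.18 to 2.37

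The only range common to all four is 2.31 to 2.37, and 1.8 lies far outside it.

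**Step 4. Power at 1.8.** The noncentrality parameter is 1.8 / 0.7071 = 2.546. With 6 degrees of freedom and a two-sided .05 test, power is 56.9%.

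**Step 5. Size of the understatement.** 1 − 1.8/2.325 = 23%, and 1 − 1.8/2.381 = 24%. For 1.8 to become detectable through adjustment, r must reach √(1 − (1.8/2.325)²) = 0.63, or 0.65 from the base of 2.381.

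**Step 6. Could another reading give 1.8?**
- Two-sided normal approximation: 1.98.
- One-sided test with 6 degrees of freedom: about 2.00.
- One-sided normal formula: 1.76, which rounds to 1.8 but contradicts both the two-sided test and the 6 degrees of freedom.
- Change score at r = 0.70: 2.325 × √(2 × 0.30) = 1.80, but this uses the baseline and so is not unadjusted.
- 6 versus 6 neighborhoods with 10 degrees of freedom: (2.228 + 0.842) × √(2/6) = 1.77, or 1.80 exactly. The Discussion mentions "an ongoing cluster-randomized controlled trial of the novel CRCEI in 12 additional communities", so an equal split there would give about 1.8. A carried-over figure is possible, but the document does not show where 1.8 came from.

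**The case against.** The best defense concedes the arithmetic and disputes its weight. Aim 2 outcomes are secondary, and the primary aim 2 model is a baseline-adjusted analysis of covariance, so 1.8 describes an analysis that is not the planned one. The number of neighborhoods was not derived from it, aim 2 data collection ended in May 2025, and the Analytic Approach stresses estimation over hypothesis testing. All of this is true, and it means that the correction changes no enrollment, model or inference. It does not make the figure right, and the authors invite others to plan from this paragraph.

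Two further points have some force. First, the aim 2 paragraph states no power of its own, so the 80% is inferred; the fit of all four adjusted figures makes that inference safe. Second, the analysis of covariance on 8 neighborhood values, with an intercept, treatment and baseline, leaves 5 residual degrees of freedom, not 6. By exact calculation with 5, the adjusted figures would be 1.99, 1.77, 1.49 and 1.31. That is a separate question about the adjusted series. It moves those figures by about 0.1 or less and does not bring the unadjusted value anywhere near 1.8.

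The idea that 1.8 came from the 12-community trial is conjecture, since other routes also land near 1.8. The conclusion does not depend on it.

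**Conclusion.** The stated unadjusted figure is wrong as written. For 4 versus 4 neighborhoods, two-sided .05 and 6 degrees of freedom, the smallest effect detectable with 80% power is 2.3 to 2.4 neighborhood-level standard deviations. The stated 1.8 is about a quarter too low, with about 57% power. The other four figures in the paragraph agree with one another and with the stated 6-degree-of-freedom design, so the error is confined to this one number.

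The conclusion assumes that the 80% target carries over from aim 1 and that effects are standardized to the between-neighborhood SD; the adjusted figures support both. Confidence is high. It is an error of reporting, not of design, but it should be corrected because it flatters the study and is offered for reuse.

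**What to change.** In the aim 2 paragraph of Sample Size and Power, replace the unadjusted 1.8 with approximately 2.3 to 2.4. The sequence then falls as the text says it should: about 2.3 unadjusted, then 1.9, 1.7, 1.4 and 1.2 as the baseline correlation rises from 0.60 to 0.85. Add one sentence that names the formula (t plus z with 6 degrees of freedom, multiplied by √(1 − r²) for adjustment), gives the 80% power target for aim 2, and says that effects are in neighborhood-level standard deviations.

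If the authors prefer the exact method, or 5 degrees of freedom for the adjusted model, they should recompute the figures with that method and say so.

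The cost is one figure and one sentence. The stated sensitivity becomes less favorable; the design, data and planned analyses stay as they are.

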### Participant Eligibility Criteria

#### Community Survey Eligibility Criteria

Eligibility for participation in the community survey requires that participants reside in the specified neighborhood, meaning that they hold an address within the preselected community or communities, and speak English. Initially, only individuals aged ≥18 years were allowed to complete the survey, but this enrollment criterion was later amended, beginning in Homewood in November 2023, to include individuals aged ≥13 years due to the importance of understanding youth experiences and perspectives.

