### Data Collection and Sourcing

For the purpose of measuring the individual-level outcomes (collective efficacy and exposure to violence) and covariates, survey data are collected across the following 3 time points: baseline (T1), the end of the phase II intervention training sessions, and comparison health sessions (T2), and follow-up approximately 8 to 12 months after baseline and to coincide with the completion of the community project for the intervention group (T3). The surveys are anonymous and linked by a personal study code that participants create by answering a series of questions that only they know the answer to at the beginning of each survey. This method of using a personal study code was selected to ensure anonymity and increase the likelihood of honest responses [40], especially for questions related to the use of violence. Baseline surveys are completed in person using paper surveys or tablets, depending on preference; T2 and T3 surveys are also completed in person on paper or a tablet or remotely using survey links that are texted or emailed to participants.

Secondary outcomes (neighborhood collective efficacy and incidence of violence) are measured at the neighborhood level. Neighborhood collective efficacy is captured through a community survey conducted at 2 points in time (T1 and T3). Incidence of violence is sourced from violent crime data for City of Pittsburgh neighborhoods obtained from the Pittsburgh Bureau of Police open data portal, while data for municipalities outside the city (eg, Wilkinsburg, Duquesne, Turtle Creek, and Braddock) are drawn from the Pennsylvania Uniform Crime Reporting system and Allegheny County sources, including police blotter data and the county’s integrated data warehouse. Incidents are geocoded, counted within neighborhood US Census tracts, and normalized by the population size for those tracts.

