#### Aim 2 (Neighborhood-Level Outcomes)

The neighborhood is the unit of analysis. The dependent variables are neighborhood-aggregated outcomes (eg, mean collective efficacy scores and rates of crime or violence). The independent variable is treatment assignment. The primary analysis will use an analysis of covariance specification, where the neighborhood-level outcome at follow-up is regressed on treatment assignment and the baseline value of the same outcome. This model provides an adjusted mean difference in follow-up outcomes between intervention and comparison neighborhoods, controlling for baseline heterogeneity. As only 8 clusters are available, models will not include random effects but will instead rely on cluster-robust variance estimators with small-sample corrections. Adjustment for additional neighborhood-level covariates (eg, baseline socioeconomic disadvantage, racial composition, and baseline crime levels) will be included cautiously in sensitivity analyses, given the limited degrees of freedom. These covariates will be added one at a time to assess the robustness of the primary results. Sensitivity analyses will also include difference-in-differences models, where the dependent variable is the change from baseline to follow-up. Results will be expressed as standardized effect sizes for comparability across outcomes and to provide planning parameters for future trials.

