## Results

Four initial neighborhoods were already participating in CRCEI prior to receiving the grant to conduct a rigorous evaluation, as described earlier. Community organizations within the 4 neighborhoods selected for comparison agreed to participate in the study. Neighborhood characteristics are similar between intervention and comparison neighborhoods (Table 1). A total of 262 participants enrolled in the study neighborhoods (n=111, 42%, in the intervention [CRCEI], with an age range of 21‐36 y per site; n=151, 58%, in the comparison health sessions, with an age range of 25‐55 y per site); all enrolled in the study and completed a baseline survey (100% participation; n=262; k=8). Most intervention and health session participants identify as Black or African American (n=170, 65%) and were born in the United States (n=227, 87%). Nearly two-thirds identify as cisgender women (n=165, 63%), and ages range from 11 to 86 years, with a median age of 39 years. Nearly half have some education beyond a high school diploma (n=123, 47%) and were living without a partner (n=123, 47%). The primary and secondary outcomes will be analyzed using the outcome measures described earlier in the methods section. A mixed methods convergent approach will be used to analyze process and implementation outcomes across quantitative and qualitative sources.

The study was funded by SAMHSA for a 5-year period starting on October 1, 2021, and by the CDC for a 4-year period starting on October 1, 2022. Data collection for aim 1 of the study was conducted through intervention and comparison participant surveys beginning on February 27, 2023, and ending on January 15, 2025. Data collection for aim 2 was conducted through intervention and comparison community surveys beginning on September 9, 2022, and ending on May 15, 2025. Data analysis for aims 1 and 2 began in April 2026, and we expect to publish the results for aims 1 and 2 in 2027. Data analysis for aim 3 began in February 2023 and ended in May 2025. Analysis of the cumulative results from the implementation science study began in April 2026, and we expect to publish the results from the implementation science study in 2027.

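### The community survey's minimum age fell from 18 to 13 during fieldwork, but the Aim 2 neighborhood mean averages all respondents, so a change in age mix can enter the treatment contrast; the shift is probably small

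*Protocol article*

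**What the plan says.** Four statements in the Protocol article have to be read together.

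- **Eligibility** (Community Survey Eligibility Criteria): "Initially, only individuals aged ≥18 years were allowed to complete the survey". Then "this enrollment criterion was later amended, beginning in Homewood in November 2023, to include individuals aged ≥13 years". Table 1 lists Homewood as an intervention neighborhood.
- **Fieldwork** (Results): "intervention and comparison community surveys beginning on September 9, 2022, and ending on May 15, 2025".
- **Outcome definition** (Secondary Outcome Measures): neighborhood collective efficacy is "aggregated to a mean value based on responses among all participants within a given neighborhood on the community survey". No age limit is attached. The same section says exposure to violence is also collected in the community survey at baseline and follow-up.
- **Analysis** (Aim 2, Neighborhood-Level Outcomes): "the neighborhood-level outcome at follow-up is regressed on treatment assignment and the baseline value of the same outcome". Difference-in-differences is a sensitivity analysis. The covariates given as examples for further sensitivity models are "eg, baseline socioeconomic disadvantage, racial composition, and baseline crime levels"; the age of respondents is not among them.

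The article gives no community-survey dates by neighborhood.

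**The concern.** The T1 mean serves as the baseline of the T3 mean. If a neighborhood was surveyed at T1 under the adult rule and at T3 under the 13+ rule, the two means refer to different populations. Any difference between youth and adults in perceived collective efficacy then appears as change over time.

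If this happens more often in one arm, part of it goes into the treatment coefficient. The difference-in-differences analysis is no check on this, because it takes the same T1-to-T3 contrast. The direction depends on whether youth rate collective efficacy higher or lower than adults, which the article does not say.

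This goes beyond a detail left to a fuller document. The article fixes the averaging rule (everyone) and also reports the eligibility change that conflicts with it. The article plans to emphasize effect magnitudes and to use standardized Aim 2 effects for planning later trials, so even a modest distortion of the estimate is worth removing.

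**Working it through.** **1. Yardstick: the plan's own detectable effects.** Sample Size and Power gives baseline-adjusted values of 1.9, 1.7, 1.4 and 1.2 at baseline–follow-up correlations r of 0.60, 0.70, 0.80 and 0.85. With 4 versus 4 neighborhoods, two-sided alpha 0.05 and 6 df:

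MDE = (t[0.975; 6] + t[0.80; 6]) × √(2/4) × √(1 − r²) = 1.90, 1.69, 1.42, 1.25.

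These agree with the stated values to within rounding.

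**2. When the age rule changed.** From 9 September 2022 to 15 May 2025 is 979 days. November 2023 is days 418 to 447, so 418/979 = 43% to 447/979 = 46% of the window.

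**3. Which sites straddle it.** The first participant baseline was 27 February 2023 (Results). In intervention sites the baseline community survey belongs to phase I, before training.
- Adding 9 to 10 weeks of training and about 6 months (Evaluation Design) puts that site's T3 at about 30 October to 6 November 2023.
- Adding 8 to 12 months (Data Collection and Sourcing) gives 28 October 2023 to 27 February 2024.
- Counting instead from the first community survey with nominal durations (3 months, 2.3 months and 6 months, about 11 in all), a T1 in September 2022 has its T3 near August 2023, before the change.

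So the earliest site sits on the boundary and cannot be classified. If the new rule applied to all survey work from November 2023, a site with T1 between about December 2022 and October 2023 would straddle it.

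**4. Youth share implied by Table 1.** Assume an even spread of ages within 0 to 17. With p the proportion aged 17 or younger, ages 13 to 17 are y = p × 5/18 of the population, and their share of those aged 13+ is s = y / (1 − p + y).
- Wilkinsburg: p = 0.2053, y = 0.0570, s = 0.0570/0.8517 = 6.7%.
- Homewood: p = 0.2398, y = 0.0666, s = 0.0666/0.8268 = 8.1%.
- The other two intervention areas give 7.3% and 7.4%.

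**5. Size of the shift.** Assumptions: two of four intervention sites and no comparison site straddle the change; the youth–adult gap g is 0.2 to 0.4 points on the 1-to-5 scale; individual SD 0.8; ICC 0.05 to 0.10.

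Shift in the arm contrast = (2/4) × s × g. This is exact for the difference-in-differences and approximate for the ANCOVA, where the fitted slope may also move.

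Neighborhood SD = 0.8 × √ICC = 0.179 (ICC 0.05) to 0.253 (ICC 0.10).

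| Youth share of respondents | Shift, points | Shift, neighborhood SD |
|---|---|---|
| 6.7% to 8.1% (Table 1) | 0.5×0.067×0.2 = 0.007 to 0.5×0.081×0.4 = 0.016 | 0.0067/0.253 = 0.03 to 0.0162/0.179 = 0.09 |
| 10% to 30% (over-represented) | 0.5×0.10×0.2 = 0.010 to 0.5×0.30×0.4 = 0.060 | 0.010/0.253 = 0.04 to 0.060/0.179 = 0.34 |

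The upper end of the first row is 0.09/1.2 = 7.5% of the smallest detectable effect in the plan.

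**The case against.** The strongest reply is that the mismatch between waves is inferred. The amendment sentence names a site as well as a date. It can mean that neighborhoods begun before Homewood stayed adult-only at both waves and later ones were 13+ at both. T1 and T3 would then agree within each neighborhood, and baseline adjustment would remove much of the difference between neighborhoods. This stands as a real possibility. It does not dispose of the point: the 8 means would still rest on two age definitions, the difference-in-differences would remove the gap only if youth share and youth–adult difference were stable over time, and an ANCOVA with slope below 1 would remove only part of it.

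A reader might also infer that the mismatch sits in the intervention arm. The intervention sites were already implementing the program when the comparison sites were chosen, which makes this likely. But no start dates for comparison surveys are given, and any comparison site that straddled the change would offset part of the shift.

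A reader might further take 0.34 neighborhood SD as the expected bias, or double it by supposing that all four intervention sites straddle. The documents support neither. A 30% youth share is far above what Table 1 implies, although recruitment in public places and at events could raise the share above proportional. Four straddling sites would require that Homewood's November 2023 survey was not its T1, which the article leaves open.

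Finally, youth were admitted deliberately, this is a secondary outcome, and analysis began in April 2026, so an adults-only main definition is a late change. That is fair, and it governs how the fix should be reported.

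**Conclusion.** The point holds in a limited form. The age change, its timing partway through fieldwork and the averaging of all respondents are stated outright. Followed as written, the rule lets a change in age mix enter the Aim 2 treatment contrast.

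Two things are probable but not shown: that some neighborhoods have an adult-only T1 and a 13+ T3, and that these lie mostly in the intervention arm. It would go too far to say that T1 and T3 certainly describe different populations in every early neighborhood.

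The size is probably small, about 0.03 to 0.09 neighborhood SD against detectable effects of 1.2 to 1.9. That rests on proportional youth response, two intervention sites and no comparison site straddling the change, a gap of 0.2 to 0.4 points, an individual SD of 0.8 and an ICC of 0.05 to 0.10. The gap, the SD and the number of straddling sites are assumptions, and the ICC values are borrowed from the Aim 1 power calculation. The shift becomes larger if youth are over-represented among respondents. The correction is worth making because it is cheap and works under either reading of the rollout.

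**What to change.** - Compute the Aim 2 community-survey outcomes (collective efficacy and exposure to violence) on respondents aged 18 or older at both waves in all 8 neighborhoods.
- Report ages 13 to 17 separately, with comparison over time only in neighborhoods where they were eligible at both waves.
- List which neighborhood-waves were adult-only, with survey dates.
- Because analysis has already begun, record this as a change made after that point and show the all-respondent result beside it.

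The cost is one sentence in the outcome definition and an age filter on data in hand. The downside is that youth, whom the survey was widened to include, leave the main Aim 2 mean. The filter does not address the separate change of sampling method after the first two intervention neighborhoods.
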